### Procedure

All persons who consult the emergency department or primary care physician after a fall receive usual care. Within two weeks after the initial presentation, written information is sent and several days thereafter, the potential participants are contacted by telephone. All actual participants (who sign informed consent) are visited at their homes by a trained interviewer within 3 months after the fall incident. During the first home visit, the fall risk profile [16], fall history, independence in activities of daily living, quality of life and physical performance are measured. All high-risk participants will report falls during at least one year using a fall calendar and receive a cost-evaluation questionnaire at 3, 6 and 12 months after the first home visit. The times to first and second fall are the primary outcome measures. One year after the first home visit, they are visited a second time to reassess the activities of daily living, quality of life and physical performance. Scores on these questionnaires and tests are used as secondary outcome measures. Furthermore, the treatment adherence and medication use are evaluated. Table 1 presents an overview of the procedure and measurements. The measurements used are described later on in this article.

**Table 1 T1:** Overview of procedure and measurements

	Months	Measurements	Purpose
1st home visit	0	fall risk profile	selection high risk participants
		fall history	assessment of fall risk factors, confounders
		activities of daily living	secondary outcome measure
		quality of life	secondary outcome measure
		medication use	assessment of fall risk factors
		medical history	assessment of fall risk factors, confounders
		physical performance	secondary outcome measure
1st follow-up	3	1st calendar sheet	primary outcome measure
		3 months cost-evaluation	primary outcome measure
2nd follow-up	6	2nd calendar sheet	primary outcome measure
		6 months cost-evaluation	primary outcome measure
3rd follow-up	9	3rd calendar sheet	primary outcome measure
2nd home visit	12	activities of daily living	secondary outcome measure
		quality of life	secondary outcome measure
		medication use	treatment adherence
		medical history	secondary outcome measure, confounders
		physical performance	secondary outcome measure
		treatment adherence	confounder, to enhance the interpretation of the results
4th follow-up	12	4th calendar sheet	primary outcome measure
		12 months cost-evaluation	primary outcome measure

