### Intervention

An extended multidisciplinary assessment starts with a visit to the geriatric outpatient clinic. A multifactorial fall risk assessment will be conducted aiming to identify modifiable fall risk factors. The assessment of fall risk factors and design of the treatment plan is based on the directives in the CBO guideline "Prevention of fall incidents in older persons" [25]. The assessment consists of a general medical and drug history, a fall and mobility history and physical examination. According to the recommendations of the CBO guideline special emphasis is placed on signs and symptoms of potentially modifiable fall and fracture risk factors such as postural hypotension, visual impairment, parkinsonism, osteoporosis, osteoarthritis, gait disorders, psychotropic and cardiac drug use, and environmental hazards. When indicated, additional diagnostic tests can be performed (e.g. laboratory tests or imaging). Based on the assessment of risk factors an individually tailored treatment regimen aimed at reduction of the fall risk is composed in close collaboration with the general practitioner of the participant. In the Netherlands, the general practitioner has a central role in the coordination of specialist's care, home care and physiotherapy among others. The collaboration facilitates the transmural continuity of care that has been lacking in most previously performed fall risk reduction trials. The multifactorial treatment can consist of, for example, withdrawal of psychotropic drugs, balance and strength exercises by a physical therapist, home hazard reduction by an occupational therapist or referral to an ophthalmologist or cardiologist. Per participant and per diagnosis the International Classification of Diseases code (ICD10) code and recommendations are reported to document the treatment regimen.

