Fall history is assessed with the fall history instrument (Carefall Triage Instrument, version 007), which is a questionnaire developed by the Academic Medical Center, the VU University Medical Center and the Erasmus Medical Center, The Netherlands. The fall history collects data on the circumstances of the last and previous falls, mobility and risk factors of bone loss and osteoporosis, social status and general health. Medical history is assessed using a questionnaire on self-reported (chronic) diseases both in the past and present. The questionnaire includes 7 major chronic diseases, i.e. chronic lung diseases, cardiac diseases, vascular diseases, stroke, diabetes mellitus, malignant neoplasms and joint disorders (i.e. osteoarthritis and rheumatoid arthritis). In addition, participants are asked to indicate any other chronic disease, including psychological diseases, which they have or have had. Medication use is assessed by directly copying the names of drugs used in the previous two weeks from the containers. The name, doses per unit, number of times taken per day, time of administration, doses per intake, purpose, prescription or over the counter (OTC) and whether the drug has been prescribed after the fall are assessed for each drug. This information is compared to medication records of the public pharmacy. Level of independence in activities of daily living (ADL) will be examined using the Barthel Index (range 0, fully dependent, to 20, fully independent) [33]. The level of functioning on more complex daily activities will be examined using a scale of instrumental ADL introduced by Lawton and Brody (range 0, fully dependent, to 8, fully independent) [34]. Quality of Life (QoL) is examined using the Dutch translations of the SF-12 and the EQ-5D. The SF-12 consists of 12 items and is a abbreviated version of the SF-36 [35]. The SF-12 has been designed and validated to measure health related QoL in large population studies [35,36]. The EQ-5D (EuroQol) has been developed to generate a general index of experienced health and for the assessment of Quality Adjusted Life Years (QALY). It is therefore suitable for economic evaluations [37]. The assessment consists of 5 items (mobility, self-care, usual activities, pain/discomfort and anxiety/depression) and a visual analogue scale (0, worst, to 100, best imaginable health state) [37]. The fall history, ADL and QoL questionnaires are sent to the participants prior to the first home visit. Participants are asked to complete these questionnaires before the home visit. The visiting researcher assists participants who are unable to complete these questionnaires independently.

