### Statistics

Data will be primarily analysed according to the intention-to-treat principle, i.e., including all randomized participants, regardless of whether they received or did not receive the intervention. Subsequently, the results of the intention-to-treat analysis will be compared with the results of an on-treatment analysis.

At baseline, differences in baseline characteristics will be compared between the intervention and control group to examine comparability between the two groups.

To examine the effectiveness of the multidisciplinary transmural care, Cox proportional hazards regression will be conducted, with time to first fall and time to second fall within one year of follow-up as outcome measures, and with age, gender and living situation as covariables. Subsequently, multiple linear regression analyses will be used to compare differences in secondary outcome measures (ADL-score, QoL, physical performance and morbidity data) at 12 months follow-up between intervention and control group.

The economic evaluation will be conducted from a societal perspective, which implies that all costs and outcomes are taken into account. The economic evaluation will involve calculating cost-effectiveness and cost-utility ratios. The incremental costs and effects of the intervention will be compared with usual care. The difference in costs of the intervention group and usual care group will be computed using bootstrapping techniques. Uncertainty ratios will be presented on cost effectiveness and cost utility planes. Acceptability curves will also be estimated. These present the probability that the intervention is cost-effective given a ceiling ratio that policy makers are willing to invest.

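### The 12-month comparison of self-reported morbidity is biased towards more disease in the intervention arm, because only that arm has a planned diagnostic work-up; the size is unknown

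*Protocol article*

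**What the plan says.** The protocol article, Statistics, uses multiple linear regression to "compare differences in secondary outcome measures (ADL-score, QoL, physical performance and morbidity data) at 12 months follow-up" between the arms. It does not define morbidity data further. In Table 1 (Procedure) the one matching entry is the medical history at the second home visit, with the purpose "secondary outcome measure, confounders".

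Baseline assessment explains the measurement: "Medical history is assessed using a questionnaire on self-reported (chronic) diseases both in the past and present". Seven disease groups are listed, one of them "joint disorders (i.e. osteoarthritis and rheumatoid arthritis"). There is also an open item, in which "participants are asked to indicate any other chronic disease, including psychological diseases, which they have or have had". The Follow-up section repeats the medical history at the second home visit.

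Under Intervention, a geriatric clinic assessment gives special emphasis to "postural hypotension, visual impairment, parkinsonism, osteoporosis, osteoarthritis, gait disorders, psychotropic and cardiac drug use, and environmental hazards". Laboratory tests or imaging may be added, and referral to an ophthalmologist or cardiologist is possible. Also, "Per participant and per diagnosis the International Classification of Diseases code (ICD10) code and recommendations are reported to document the treatment regimen". The Usual care section says that the control condition mainly treats the consequences of the fall, and that systematic assessment of risk factors in primary care is only occasional.

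**The concern.** A self-report of chronic disease measures two things together: whether the disease is present, and whether the participant has been told of it. The intervention acts directly on the second. An intervention participant whose osteoarthritis, osteoporosis or parkinsonism is first recognised at the geriatric clinic can report it at 12 months. A control participant with the same unrecognised condition cannot.

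The outcome therefore partly measures delivery of the intervention. Randomisation balances true disease at baseline, and intention to treat keeps the groups as randomised, but neither equalises detection after randomisation. Adjusting for the baseline questionnaire would not do so either, because the new knowledge arises later. At stake is a published secondary result in which better case-finding is read as increased morbidity.

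**Working it through.** **1. Does the overlap exist?** Setting the Intervention section beside the questionnaire:

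| Looked for, or open to discovery, in the work-up | Place in the questionnaire |
|---|---|
| Osteoarthritis | Named within a listed group (joint disorders) |
| Cardiac disease (cardiac drug review, possible cardiology referral) | Listed group; discovery is possible but not a stated aim |
| Osteoporosis, parkinsonism | Only through the open item |
| Postural hypotension, visual impairment | Open item, if participants regard them as chronic diseases; not stated |
| Lung disease, diabetes, cancer | Listed groups, but not stated targets |

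The overlap is real but partial.

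**2. The plan's own figures.** None is given for morbidity. The sample size concerns falls: 57/(1 − 0.30) = 81.4, rounded up to 82 per arm, as stated. From that section I take only the planned 100 per arm and the 30% drop-out allowance, which leaves 100 × 0.70 = 70 per arm at 12 months.

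**3. How large could the bias be?** All rates below are assumptions, with no true difference in disease and a two-sided 5% test (the article does not state sidedness). The probabilities are for a significant excess in the intervention arm; without bias this is 2.5%.

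*One disease, with different shares known to participants.* Reported proportion = true prevalence × share known. With p̄ the mean of the two proportions, SE₀ = √(2p̄(1−p̄)/n) and SE₁ = √((p₁(1−p₁)+p₂(1−p₂))/n), the probability is Φ((difference − 1.96·SE₀)/SE₁).

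| True prevalence | Share known, control v intervention | Reported | Ratio | n = 100 | n = 70 |
|---|---|---|---|---|---|
| 20% | 70% v 80% | 14% v 16% | 1.14 | 6% | 5% |
| 20% | 70% v 90% | 14% v 18% | 1.29 | 12% | 9% |
| 20% | 50% v 90% | 10% v 18% | 1.80 | 37% | 27% |
| 40% | 70% v 80% | 28% v 32% | 1.14 | 9% | 7% |
| 40% | 70% v 90% | 28% v 36% | 1.29 | 23% | 17% |
| 40% | 50% v 90% | 20% v 36% | 1.80 | 72% | 56% |

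*A disease count, closer to the planned linear regression.* The probability is Φ(d/(SD·√(2/n)) − 1.96), where d is the extra diagnoses per person.
- d = 0.1, SD 1.3, n = 100: 0.1/(1.3 × 0.1414) = 0.54, giving 8%.
- d = 0.5, SD 1.0, n = 100: 0.5/0.1414 = 3.54, giving 94%.
- The same two cases at n = 70 give 7% and 84%.

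*Newly reported disease.* Suppose 5% of controls report a new disease and the work-up adds 10 percentage points.
- 15% v 5%, n = 100: z = 0.10/√(0.10 × 0.90 × 2/100) = 0.10/0.0424 = 2.36. This is the expected z; the chance of significance is about 66%.
- 15% v 5%, n = 70: z = 0.10/0.0507 = 1.97, a chance of about 50%.
- If the work-up adds 30 points (35% v 5%, n = 100): z = 0.30/0.0566 = 5.30.

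The direction is the same throughout. The size depends almost wholly on the assumed rates.

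**The case against.** The strongest reply is that the outcome is not fully defined. The article says only morbidity data; the running text of the Procedure section names only daily activities, quality of life and physical performance as secondary outcomes; and the derivation may be set out in a fuller document. This limits what can be claimed, but it does not remove the problem. Whether the outcome is derived as current, ever-reported or newly reported disease, it still depends on what the participant has been told. No choice of model repairs that.

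Several stronger readings are tempting and are not supported:

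- *A reader might infer that the measure counts lifetime disease and so can only rise.* The questionnaire asks about past and present disease, but nothing says that the outcome is a lifetime count.
- *A reader might infer that the comparison cannot show benefit, or is bound to look like harm.* Real benefit could offset the bias, and the milder assumptions above barely raise the false-positive rate.
- *A reader might infer that a false significant result is nearly assured.* An expected z of 2.36 means about a 66% chance of significance, or about 50% after the planned drop-out, and the rates behind it are assumed.
- *A reader might take the ICD-10 coding as evidence of the mechanism.* The article says that it documents the treatment regimen, not that it feeds the questionnaire.
- *A reader might propose admissions from the cost questionnaire as a ready substitute.* That questionnaire also registers costs of preventing a new fall, so care prompted by the work-up could enter it. The article mentions the aim of surgical procedures but no reason for admission.

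It also stands that this is one secondary outcome among several.

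**Conclusion.** The point holds as one of biased ascertainment. The 12-month morbidity comparison, as planned, leans towards apparently higher morbidity with intervention. The mechanism is clearest for osteoarthritis, possible for cardiac disease, and open for osteoporosis and parkinsonism through the free item.

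The conclusion rests on two readings: that morbidity data means the self-reported medical history, the only match in Table 1; and that the work-up reveals more disease than it rules out. The documents do not give the size. The illustrative chance of a false significant excess at 100 per arm runs from about 6% to 72% for a single disease and from 8% to 94% for a count. The bias may be small and may be offset by real benefit. The primary fall outcomes and the sample size are unaffected. This is a worthwhile, low-cost correction to a secondary outcome and does not threaten the trial's main result.

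**What to change.** 1. In Statistics, remove self-reported morbidity from the secondary outcomes tested between arms. Report 12-month diagnoses descriptively by arm, with a sentence stating that only the intervention arm had a planned diagnostic work-up.
2. In Table 1, relabel the 12-month medical history to match.
3. If a tested morbidity comparison is kept, restrict it to events that do not depend on the work-up and can be identified in both arms as consequences of a new fall. An example is surgery whose recorded aim is treatment of a fall injury. Use admissions only if their reason is recorded.

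The first two steps change wording only and cost one tested secondary outcome. The third may need an added question on the reason for admission.

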#### Follow-up

At the first home visit the participants receive a fall calendar [16]. For the period of one year, the participants tick per week whether they did or did not fall during that week. A fall is defined as an unintentional change in position resulting in coming to rest at a lower level or on the ground [41]. Once per 3 months the participants return a calendar sheet by mail. When no sheet is received, or when the sheet is completed incorrectly, we inquire by telephone whether, and if yes, when the participant has fallen in the past 3 months.

The cost-evaluation questionnaire registers the costs made to prevent a new fall or the consequences of a new fall. The questionnaire assesses: the number of visits to physicians, therapists or day care centres; amount and aim of surgical procedures; number of days of admission to a hospital, home or nursing home; purchase of aids and adaptations in the home environment. The questionnaires are conducted 3, 6 and 12 months after the first home visit. The 3 and 6 months questionnaires are sent by mail and apply to the preceding 3 months. The 12 months questionnaire is assessed during the interview of the second home visit. This questionnaire applies to the preceding 6 months. When no questionnaire is received, or when it is completed incorrectly, the questionnaire will be completed by telephone.

During the second home visit, one year after the first visit, the same physical performance tests are conducted along with a reassessment of fall related healthcare costs, medical history, medication use, quality of life and activities of daily living. In addition, in the intervention group, adherence to the treatment regimen is evaluated. Treatment adherence in the intervention group is evaluated per recommendation given. Recommendations regarding changes in medication are evaluated by reassessing the medication use as described above. Adherence to all other recommendations (such as referrals to physical therapy or cardiologist) is assessed by asking whether, to what extent, and how the recommendations of the intervention were effected. The information from the participant is completed with information from the rapports of the involved specialists.

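### The economic evaluation is declared societal and covering all costs, but the cost questionnaire is described as covering only fall-related costs

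*Protocol article*

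**What the plan says.** The Statistics section sets the perspective and defines it: "The economic evaluation will be conducted from a societal perspective, which implies that all costs and outcomes are taken into account". It then plans cost-effectiveness and cost-utility ratios against usual care, a bootstrapped cost difference, cost planes and acceptability curves.

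The Follow-up section describes how costs are collected. Its lead sentence sets the scope: "The cost-evaluation questionnaire registers the costs made to prevent a new fall or the consequences of a new fall". The items listed are "the number of visits to physicians, therapists or day care centres; amount and aim of surgical procedures" and "number of days of admission to a hospital, home or nursing home; purchase of aids and adaptations in the home environment". On timing, "The 3 and 6 months questionnaires are sent by mail and apply to the preceding 3 months"; the third questionnaire is completed at the second home visit and looks back six months. That visit repeats the physical tests "along with a reassessment of fall related healthcare costs".

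Table 1 (Procedure section) labels the cost evaluation a primary outcome measure at 3, 6 and 12 months, although the text names only the times to first and second fall as primary. The baseline measurements include the EQ-5D, presented as a general health index suited to QALYs and economic evaluation.

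**The concern.** The article states both what the evaluation claims to cover and what the instrument collects, and the two differ. This is not a detail left to a fuller protocol: each statement is made outright, and the restriction to falls appears twice.

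Cost-effectiveness is one of the two stated aims of the trial. A policy maker who reads an acceptability curve labelled societal will take it that costs outside falls have been counted. If they have not, the curve answers a narrower question than its label says, and any cost or saving that the intervention causes outside falls is lost.

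**Working it through.** No figure in the article bears on this point, so the check sets the statements side by side.

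| Element | Where | Scope |
|---|---|---|
| Perspective | Statistics | All costs and outcomes |
| Cost questionnaire, lead sentence | Follow-up | Preventing a new fall, or its consequences |
| Costs at the 12-month visit | Follow-up | Fall-related healthcare |
| Cost items | Follow-up | Visits, surgery, admission days, aids, home adaptations; no fall qualifier on the items themselves |
| Utility measure | Baseline assessment | General health (EQ-5D) |

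**Step 1: cost difference.** Write the between-arm difference in all costs as ΔC(all) = ΔC(fall) + ΔC(other). The Statistics section promises ΔC(all). The Follow-up section, as written, yields ΔC(fall). The two agree only if ΔC(other) = 0.

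**Step 2: can ΔC(other) be assumed to be zero?** The article gives no ground for it. The Intervention section names measures such as "withdrawal of psychotropic drugs, balance and strength exercises by a physical therapist", as well as extra diagnostic tests and referral to an ophthalmologist or cardiologist. The care itself may count as a cost of preventing a fall. Its later consequences for use of care need not be fall-related, and they would arise mainly in the intervention arm.

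**Step 3: ratios.** For an effect difference ΔE, the planned ratio is ΔC(fall)/ΔE, where the stated perspective requires [ΔC(fall) + ΔC(other)]/ΔE. If the effect is falls, numerator and denominator at least share a scope. If the effect is QALYs from the EQ-5D, they do not: general health gains are counted below the line and only fall-related costs above it. That the EQ-5D supplies the QALYs is an inference from its description; the Statistics section does not name the utility measure.

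**Step 4: can the planned methods repair this?** No. Bootstrapping, cost planes and acceptability curves describe sampling uncertainty in the costs that were recorded. They say nothing about costs that were not.

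**Step 5: label.** The Follow-up section is not uniform about its own scope. The 12-month wording refers to healthcare, yet aids and home adaptations go beyond healthcare. An accurate restricted label is therefore fall-related costs including those items, not fall-related healthcare costs alone.

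**The case against.** The strongest reply is that the form itself is not shown. The listed items carry no fall qualifier, and recording the aim of surgery fits a form that captures all use and leaves classification to the researchers. Aids, home adaptations and day care also reach beyond a healthcare payer, so a societal view limited to fall-related costs is a defensible design. All of this stands. It means the conflict may be resolved from either side, but it does not remove the conflict, because the text claims all costs and describes fall-related ones.

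Three stronger readings are tempting and are not supported.

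- **Biased attribution by arm.** A reader might infer that participants, knowing their arm, will label the same visit as fall-related more often under the intervention. If shares f1 and f0 of an identical all-cause cost C were so labelled in the intervention and usual-care arms, the false difference would be (f1 − f0) × C, and with f1 above f0 it would count against the intervention. But the article does not say that participants decide what is fall-related, nor what each arm is told, and both arms complete the fall risk profile and fall history. None of f1, f0 or C is given. It is a possible risk, not a demonstrated bias.
- **Missing items.** Drugs, home care and informal care are not listed, but an article may condense a questionnaire into one sentence. Drug names and doses are recorded and compared with pharmacy records. Table 1 gives that recording other purposes, but nothing bars its use for costing.
- **All-cause costing is required.** All-cause costs are noisier, and the trial was sized on fall incidence. The choice is a trade-off, and fall-related costing is acceptable if it is labelled as such.

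**Conclusion.** The point holds as a contradiction within the article. By its own definition of the societal perspective, the economic results as planned cannot support a conclusion about all costs, and the cost-utility ratio would combine fall-related costs with a general-health effect.

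The size of the discrepancy is ΔC(other), which cannot be computed from the article. The conclusion assumes that the Follow-up section describes the form correctly and, for the cost-utility ratio, that QALYs come from the EQ-5D. If the form records all use regardless of cause, the error lies in the Follow-up text and not in the perspective. The comparison of times to first and second fall is not touched.

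**What to change.** Reconcile the two sections before the analysis begins, which the article places after follow-up ends in July 2008.

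1. **If the form is restricted as described:** restate the perspective, and every cost difference, ratio, plane and curve, as covering fall-related costs including aids and home adaptations. Remove the claim to all costs. State beside the cost-utility ratio that its costs are fall-related and its effect is general health.
2. **If the form records visits and admissions regardless of cause:** correct the Follow-up text, use all recorded costs in the main analysis, and report fall-related costs as secondary.
3. **In either case:** where feasible, cost drugs from the medication and pharmacy records already consulted. If participants decide what counts as fall-related, acknowledge possible differential attribution by arm as a limitation.

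Changing the form during the trial is not advised as the main remedy. Inclusion began in April 2005, so earlier and later participants would have costs defined in two ways.

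The first route costs a few sentences and a narrower stated conclusion. The second costs a text correction and noisier totals. Drug costing adds some data work.
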